**Figure 1 Fig1:**
[figure not shown]
**Trial flow diagram.**

### Participants’ eligibility

For the current study, we will recruit caregiving partners, children, and children-in-law. Inclusion criteria are that the caregiving relative has key responsibility for the care of the person with dementia and that the person with dementia has at least low grade dementia according to medical diagnosis. Exclusion criteria are that the caregiving relative receives ongoing psychotherapeutic treatment, has a severe physical illness or medically diagnosed psychiatric disorder, and that the person with dementia is institutionalized or institutionalization is planned for the next 6 months.

### Recruitment

The recruitment of the study participants will be nationwide with a special focus on Berlin, Jena and Munich, as the F2F intervention will only be performed in these centers. For recruitment, different public relations methods will be used: printed information materials available at cooperation partners (clinics, practices, home support services), editorial articles in regional and national newspapers, television and radio interviews, a project homepage (www.teletandem.uni-jena.de), and presentations of the study in groups for family caregivers.

### Ethical approval

Ethical approval was obtained from the Ethics Commission of the Friedrich-Schiller-University Jena. Participants will be informed about the content, purpose, and procedure of the study, and written informed consent will be obtained. The person with dementia will also receive information on the study. An indirect positive effect is expected on the well-being of the persons with dementia. In the previous study, the intervention did not pose any risks. No negative impact on the study participants is expected, since in case of severe depression or a suspected suicide intention, the caregiving relatives will be transferred to the institutions of usual care. Personal data will be stored separately from research data. The first, second, and third assessment (T0, T1, and T2) will be linked to each other by means of a researcher generated identification code. All personal data will be deleted after completion of the study. Participation in the study will be voluntary and the participants may withdraw consent at any time.

### Procedure

Once potential participants contact the study center, they will be screened for meeting the eligibility criteria in a manual-based telephone interview. Additionally, information on the participants’ sex as well as the possibility of taking part in F2F will be assessed in this screening.

After a positive screening, all potential study participants will receive an information package including information about the study, informed consent forms for study participation and data processing as well as for telephone contact, information for the person with dementia, and several leaflets on dementia and caregiving.

For the first assessment, participants will be contacted by phone, an appointment for the telephone interview will be made for about two weeks later, and the questionnaires will be sent out. This survey technique is used because a mostly elderly study population is expected. In addition, the acceptance of the survey is to be improved and the risk of missing data or dropout to be reduced. In the telephone interview, comprehension difficulties and unanswered questions will be discussed and the questionnaires will be reviewed for completeness. After the telephone interview, the questionnaires will be returned in a return envelope.

Participants will be allocated to the three study groups after finishing the baseline assessment (T0). To ensure a sufficient number of caregivers taking part in F2F, all participants living in Berlin, Jena or Munich for whom attendance is possible will be allocated to the F2F intervention, as long as their mobility is given. A bias is not expected because the participants will not be aware of being exclusively allocated to F2F, as they will be informed about being randomized to one of the three groups. The random number generator Random.org will be used for randomization. After being informed about their group allocation, participants in the intervention groups will receive the therapy sessions. After 6 months, when the therapy is finished, the T1 assessment will be conducted. After another 6 months, the T2 assessment will be conducted. The control group will receive an allowance for participation of 40 EUR, which will be transferred after completion of the study.

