## Methods/Design

### Design

This study is a non-blinded two-armed parallel randomized controlled trial with a third non-randomized group. Participants will be asked whether they reside in the area of a study center and can participate in the F2F. If this is the case, they will be assigned to the F2F group. If this is not the case, they will be randomly assigned to the TEL group or usual care. Random allocation will be on a 1:1 ratio basis but separated for gender and will take place after the baseline assessment. All participants will receive information materials on care and dementia. Assessments will be conducted at baseline (T0), post intervention (T1) and a 6-month follow-up (T2) (Figure 1). The TEL group will receive 12 psychotherapy sessions on the phone, whereas the F2F group will receive 12 psychotherapy sessions in direct contact in one of the participating treatment centers.

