### Data analysis

The data will be analyzed with SPSS version 22.0 (IBM Corp., Armonk, NY) and MPlus version 7.0 (Muthén & Muthén, Los Angeles, CA). Data cleaning and analyses will be performed using SPSS/Mplus syntax operations. Possible baseline differences between trial arms will be statistically tested and further analyses will be adjusted for imbalances in the baseline scores. The primary analysis will be by intention to treat. For the primary outcomes, analyses will be corrected for multiple testing.

As sensitivity analyses, completers of all assessments will be analyzed separately. Hypotheses tests will be performed at *α*=.05. The numeric outcomes will be analyzed using analyses of variance; categorical outcomes will be analyzed using *χ*^2^-tests. Additionally, latent change model analyses will be performed for continuous longitudinal outcome data. To handle missing data, full information maximum likelihood estimation will be conducted in MPlus. As part of the questionnaire adaptation, factor, reliability, and correlation analyses will be performed.

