## Discussion

This study will evaluate whether TEL improves depressiveness, burden of care, health complaints, and problem-solving ability compared to usual care and assess whether TEL is as effective as F2F. One strength of this study is its robust design and follow-up assessment allowing evaluation of the long-term effects of TEL. For the first time, it will be possible to test intervention effects of TEL in established care services.

However, there will also be several challenges in this study. In particular, enrolling a sufficiently large sample in the F2F group will be a major difficulty, which we hope to overcome by recruiting via different media and by directly assigning participants to F2F.

The F2F sample will be especially selective, as it will consist of an exclusively urban and mobile population. Since possible F2F participants will be selected from the overall recruited sample, the remaining subsample being randomized will potentially be more rural and less mobile than the original sample recruited.

To ensure adequate and homogeneous application of therapeutic strategies, extensive training prior to implementation, application through CBT-qualified therapists, regular supervision (4 to 6 times per year) and documentation of the implementation will be essential strategies. To determine treatment integrity, independent CBT-qualified therapists will assess psychotherapeutic competence and adherence in randomly selected audio and video recordings of the sessions.

In case the intervention is terminated prematurely, an attempt will be made to continuously include the participant in the data collection. To avoid selective dropout in the control group, this group will receive an incentive. Blinding is not possible in the design of the proposed study, since both the family caregivers and the therapists will know whether a therapy is conducted. To nevertheless guarantee an independent assessment of intervention efficacy, the data collection will be performed by researchers who are not involved in the therapy.

In summary, this will be the first study to test the implementation of telephone-based cognitive-behavioral therapy in established care provision structures in a randomized controlled trial. If TEL proves to be effective in improving primary outcomes, our results will be relevant to practice. Hence, TEL could be used on a large scale. Thus, the results of the study will be used to improve support services for family-caregivers.

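### TEL versus F2F is confounded by the allocation rule, and participants' unawareness of that rule is no ground for expecting no bias

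*Protocol article*

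**What the plan says.** All of this is in the Protocol article.

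- **Design** describes a "non-blinded two-armed parallel randomized controlled trial with a third non-randomized group". Caregivers are asked whether they live in a centre's area and can take part in F2F; those who do and can are assigned to it. For everyone else: "If this is not the case, they will be randomly assigned to the TEL group or usual care".
- **Procedure** gives the same rule with a mobility condition added: "all participants living in Berlin, Jena or Munich for whom attendance is possible will be allocated to the F2F intervention, as long as their mobility" (the quotation stops at that condition). It then says: "A bias is not expected because the participants will not be aware of being exclusively allocated to F2F". The supporting reason is that "they will be informed about being randomized to one of the three groups".
- **Discussion** says: "The F2F sample will be especially selective, as it will consist of an exclusively urban and mobile population". It adds that those left for randomisation may be more rural and less mobile than the whole recruited sample.
- **Background** makes the equivalence of TEL and F2F secondary objective (1). The Abstract and the Discussion repeat that aim.
- **Data analysis** plans tests for baseline differences between arms and adjustment for imbalances in baseline scores. "The numeric outcomes will be analyzed using analyses of variance", with latent change models in addition. Residence, mobility and care situation are not named as adjustment variables.

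**The concern.** The no-bias statement rests on one argument: participants do not know that F2F is filled directly. That argument concerns what people expect or how they might react to their allocation. It does not concern who is in each group, and group membership is what the allocation rule determines.

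The selection factors are plausibly prognostic on the article's own reasoning. The Background says that having to leave the person with dementia, poor mobility and distance hinder the use of support, and it links reduced mobility to older caregivers. Use of professional assistance is a secondary outcome. Health complaints, which include fatigue, heart problems and joint pain, are a primary outcome.

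The answer to secondary objective (1) is at stake. A difference between the two populations could appear as a difference between delivery modes. It could equally mask a real one and give false support to the claim that TEL is as effective as F2F.

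**Working it through.** **1. The plan's own figure.** The Sample size section gives 82 per group for a small effect, two groups, three measurements, α = .05, power .80 and ρ = .50. The article gives no number for the small effect; f = 0.10 is assumed here. For the group-by-time interaction:

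- λ = f² × N × m / (1 − ρ) = 0.01 × 164 × 3 / 0.5 = 9.84
- df = (2 − 1)(3 − 1) = 2 and (164 − 2)(3 − 1) = 324
- Power is 0.805 at N = 164 and 0.7998 at N = 162, so 82 per group reproduces. The between-group main effect would need 263 per group.
- Dropout: 82 / 0.7 = 117.1, rounded up to 118, as stated.

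These figures are sound and the point changes none of them. They do show that the sample size corresponds to a contrast in change over time, which matters in step 3.

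**2. Overlap on the assignment criterion.** Let C be the criterion from Design and Procedure: lives near a centre, can attend, is mobile.

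| | C met | C not met |
|---|---|---|
| Goes to F2F | all | none |
| Randomised to TEL or usual care | none | all |

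So P(F2F | C met) = 1 and P(F2F | C not met) = 0, until F2F reaches its cut-off of 118. The article does not say how later caregivers who meet C are handled. If they were randomised, some overlap would arise then. Before that point there is none, and no regression or weighting model can create it.

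**3. What the TEL–F2F contrast contains.** Write a group's mean after therapy as μ (prior level) + τ (course without therapy) + θ (therapy effect), with subscripts T for TEL and F for F2F.

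- Contrast of post-therapy levels: (μT − μF) + (τT − τF) + (θT − θF).
- Contrast of changes from T0: (τT − τF) + (θT − θF).

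A stable level difference drops out of the change contrast. A difference in course does not. Usual care informs τT because it is randomised against TEL. No untreated group is drawn from caregivers who meet C, so nothing in the design informs τF. In addition, θT and θF are effects in different populations, so their difference need not be the effect of delivery mode.

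**4. Does unawareness remove any of these terms?** It may limit differences in expectation. It leaves μ, τ and the populations behind θ unchanged.

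**5. Does the stated adjustment remove them?** Adjusting for imbalanced baseline scores addresses part of μT − μF, and only when a baseline test triggers it. It does not address the selection factors or a difference in course.

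**6. Can a size be given?** For a comparison not adjusted for a prognostic factor, the bias is roughly the group difference on the factor (in SD) times its correlation with the outcome. The article gives neither. Assumed differences of 0.2 to 0.8 SD and correlations of 0.1 to 0.5 give 0.2 × 0.1 = 0.02 SD up to 0.8 × 0.5 = 0.40 SD, with either sign. A twenty-fold range of unknown sign shows only that the document does not fix a size.

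**The case against.** **Disclosure.** The article does not hide the design. It labels F2F non-randomised, states the rule more than once and admits selectivity in the Discussion. This stands, and no reader is led to think that F2F is randomised. But the label is not carried through to secondary objective (1), and the Discussion treats selectivity as a matter of sample composition without drawing the consequence for the comparison.

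**A narrower reading of bias.** Since the only reason given is unawareness, the sentence may have been meant for expectation or self-selection effects. That is a fair reading, and narrowing the sentence would remove the conflict. As written, it is unrestricted.

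**The SAP.** A full covariate list is commonly left to the analysis plan, which is not shown. Its absence is therefore not the point. The point is that the article affirms a wrong premise and states an adjustment rule that does not match the selection.

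**Readings that go too far:**

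- A reader might infer that the main result is compromised. It is not: TEL versus usual care is randomised within the same pool, and only its generalisability is touched.
- A reader might infer a bias of some tenths of an SD, comparable with the d = 0.14 to 0.41 in the Sample size section. No such figure can be drawn from the article. That range describes caregiver interventions, not a TEL–F2F difference, and a level difference does not pass in full into a change contrast.
- A reader might picture F2F as urban and TEL as rural. Recruitment is nationwide, so TEL can include people in other cities and mobile people far from a centre.
- A reader might look to TEL participants in the Jena, Berlin and Munich areas as a better comparator. Before the cut-off, these are the local caregivers who cannot attend, so the restriction would sharpen selection on attendance and mobility.

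**Conclusion.** The no-bias statement is wrong for TEL versus F2F. The groups are formed by residence, ability to attend and mobility, and the article's Discussion concedes the selectivity that its Procedure section sets aside. Secondary objective (1) is confounded by design, and the stated adjustment for baseline scores mitigates this only in part. The direction and size of the bias cannot be derived from the article. The primary objective and the sample size are unaffected.

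The conclusion rests on the allocation rule being applied as written. That the selection factors bear on the outcomes is an inference from the article's own rationale, not something it demonstrates.

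Separately, telling participants that they are randomised to one of three groups does not match the non-randomised allocation in Design. A reader might infer that the information sheet is wrong. The sheet is not shown, so what can be said is that the two statements must be reconciled.

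**What to change.** 1. In Procedure, strike the no-bias sentence or restrict it to expectation effects, and make it consistent with the Discussion.
2. Analyse TEL versus F2F separately from the randomised arms and label it a non-randomised comparison wherever objective (1) is reported.
3. Fix the adjustment set in advance, independent of baseline tests: T0 outcome scores and the T0 background variables already collected (socio-demographics, caregiver diseases, care conditions, dementia type, services used). The article's list of background variables names neither urban or rural residence nor mobility as such, so this set covers them only indirectly.
4. State that there is little or no overlap on the assignment criterion itself, that residual confounding therefore remains after any adjustment, and that the finding on TEL relative to F2F is an association only.
5. Reconcile the statement that participants are told they are randomised to one of three groups with the allocation described in Design.

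**Cost.** Items 1 to 4 need rewording and some analysis work on data already planned, and they lead to a more cautious conclusion on TEL versus F2F. If item 5 means changing the participant information, it may need ethics review. Telling participants the rule could also bring back the expectation effects that the Procedure section tries to avoid, and that trade-off should be stated.

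### Participants are to be told of a three-group randomization that nobody undergoes, and the claim that F2F allocation introduces no bias rests on it

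*Protocol article*

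**What the plan says.** The Design section of the protocol article states: "This study is a non-blinded two-armed parallel randomized controlled trial with a third non-randomized group". Caregivers who live near a centre and can attend are assigned to F2F. For everyone else the rule is: "If this is not the case, they will be randomly assigned to the TEL group or usual care". On the ratio it adds: "Random allocation will be on a 1:1 ratio basis but separated for gender".

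The Procedure section repeats the F2F rule: "all participants living in Berlin, Jena or Munich for whom attendance is possible will be allocated to the F2F intervention", subject to their being mobile. It then says that no bias is expected, because "the participants will not be aware of being exclusively allocated to F2F", and gives the reason: "as they will be informed about being randomized to one of the three groups".

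Two further statements matter. At the screening interview, before the information package is sent, "information on the participants’ sex as well as the possibility of taking part in F2F will be assessed in this screening". Under Ethical approval, "Participants will be informed about the content, purpose, and procedure of the study, and written informed consent will be obtained".

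**The concern.** The article says what participants will be told about allocation, and what they will be told is not what will happen. This is not loose wording: the inaccurate description has a stated purpose, to keep F2F caregivers unaware of their fixed assignment.

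Two things are at stake. The first is consent: whether a person is randomized at all, and between which options, is a central part of what that person agrees to. The second is the inference drawn from the concealment. The article treats participants' unawareness as grounds for expecting no bias. One of its secondary objectives is to judge whether TEL is as effective as F2F, and a reader who accepts the no-bias claim would give that comparison more weight than a non-randomized one can carry.

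**Working it through.** The plan gives no figure for what participants are told, so the check sets the stated allocation rule beside the stated information.

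**Step 1: the actual rule (Design and Procedure sections).** Chance of each group, by route:

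| Caregiver | F2F | TEL | Usual care | Three-group randomization? |
|---|---|---|---|---|
| Can attend a centre, F2F places open | 1 | 0 | 0 | No |
| Cannot attend | 0 | 1/2 | 1/2 | No |
| Can attend, F2F cut-off of 118 reached | not stated | not stated | not stated | None described |

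A randomization to one of three groups would give each person a positive chance of all three. Neither stated route does.

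**Step 2: could it be true in aggregate?** If F2F filled to its cut-off, the three groups would each hold 118 / (118 + 118 + 118) = 1/3 of participants. That is a split of the final sample, not a chance that any individual faced. A caregiver who can attend has no chance of usual care while F2F is open, and one who cannot attend has no chance of F2F.

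**Step 3: who is misinformed?** The sentence about what participants are told directly follows the one on caregivers who can attend, so it covers them for certain. Extending it to the others rests on two things: the words say three groups, and the Procedure section has an information package going to all potential participants after a positive screening. This is a reasonable inference, but it is not stated. The counts are up to 118 people on the narrow reading, plus 2 × 118 = 236 planned randomized participants on the wider one.

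**Step 4: consistency with the consent statement.** The Ethical approval section promises information about the study procedure. The allocation rule is itself set out under the heading Procedure. Informing participants about the procedure and describing its allocation step wrongly cannot both hold.

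**Step 5: does unawareness support the no-bias claim?** It may limit what participants expect when they complete the baseline assessment. It does nothing about who enters F2F, which depends on residence, ability to attend and mobility. The Discussion section concedes the point: it describes the F2F sample as highly selected, urban and mobile, and the randomized remainder as potentially more rural and less mobile.

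**Step 6: is the sample size affected?** No. The stated inputs are two groups, three measurements, α = .05, power .80 and ρ = .50. Taking f = 0.10 for a small effect (an assumption) and the group-by-time test, λ = f²·N·m/(1 − ρ) = 0.01 × 164 × 3 / 0.5 = 9.84, with 2 and 324 degrees of freedom. Power is 0.805 at N = 164 and 0.7998 at N = 162, so 82 per group reproduces. For dropout, 82 / 0.70 = 117.1, rounded up to 118. None of these inputs depends on what participants are told.

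**The case against.** The strongest defence has four parts.

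- **The primary comparison is sound.** TEL versus usual care is genuinely randomized 1:1, and nothing here disturbs it. This stands.
- **The sentence may concern only F2F caregivers.** This is the most natural reading of its position, and the consent form is not shown. It limits the certain part of the finding to that group. The misdescription remains there, although these caregivers receive therapy rather than face an undisclosed risk of receiving none.
- **The ethics committee approved the study, and may have approved incomplete disclosure.** That cannot be ruled out from a condensed article, so the point is not that approval is lacking. The article nevertheless makes two statements that conflict and does not reconcile them.
- **The choice was deliberate, and participants learn their group before therapy and may withdraw.** This is true, but learning the group afterwards does not correct the description on which consent was given.

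A reader might go further and infer that participants are given wrong odds, for example that everyone is told of a one-in-three chance of usual care. The article reports no odds told to participants, so no understatement in percentage points can be derived. A reader might also expect homebound caregivers to decline because they fear being sent to a centre, or usual-care participants to drop out in disappointment. Nothing in the article supports either effect. It provides a 40 EUR allowance for the control group, meant to avoid selective dropout there, and allows for 30% dropout.

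**Conclusion.** The point holds as a false description of the allocation mechanism. It is certain for caregivers assigned to F2F (up to 118). For the 236 planned randomized participants it is conditional on their receiving the same statement. It conflicts with the commitment under Ethical approval to inform participants about the procedure.

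The no-bias claim fails on either reading, since unawareness cannot remove selection by residence and mobility and the article's own Discussion admits that selection. The consequence is confined to consent and to the secondary TEL versus F2F comparison. The size of the selection bias cannot be calculated from the article. The randomized primary comparison and the sample size stand as written.

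**What to change.** 1. Replace the three-group statement with the actual allocation rule. The possibility of F2F is already on record from screening, before the package is sent, so two information sheets can be used. One would say that the caregiver is assigned to F2F without randomization; the other, that allocation is 1:1 between TEL and usual care, with no F2F.
2. State what happens to caregivers who can attend once the F2F cut-off of 118 is reached, and word the first sheet to match. Without this, that sheet could be untrue for late enrollees.
3. If the sponsor prefers to keep the concealment, state in the protocol that the ethics committee explicitly approved incomplete disclosure, and describe the debriefing.
4. In either case, delete the claim that no bias is expected, and describe TEL versus F2F as a non-randomized comparison subject to selection by residence and mobility.

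For the first option the cost is a revised information sheet and an ethics notification. There are two downsides. F2F participants may know before baseline that they will receive therapy, which could affect their baseline ratings; this is confined to the non-randomized group. Also, a disclosed rule could become known to later callers before screening, since recruitment runs through media, a homepage and caregiver groups, so two sheets reduce the tailoring of answers about attendance but do not exclude it. The TEL versus usual-care randomization and the target of 118 per randomized group do not change.
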